## Methods

### Research design

Our study is designed as a naturalistic, multi-center prospective cohort study among youth seeking help in addiction treatment to investigate the study objectives mentioned above.

We will recruit youth aged 16 to 22 years (*N* = 420) who enter addiction treatment at ten participating treatment organizations from a total of 13 organizations in the Netherlands. Participants will be assessed on a range of measures related to substance use and SUD, comorbid mental health problems and social functioning at treatment-entry (baseline), end of treatment, and 2 and 4 years post-baseline. Study-inflow of participants consists of consecutive admissions, and will be prestratified by treatment organization to ensure a nationally representative sample. Treatment consists of treatment as usual, as provided by the participating addiction care organizations, to maximize generalizability of the study findings to everyday clinical practice. Analyses will be conducted following an intention-to-treat approach.

This study was funded by The Netherlands Organization for Health Research and Development (60–63,600–98-317) and was approved by the Medical Ethical Board of the Leiden University Medical Center (NL65903.058.18; file number P18.175). Trial registration: NL7928.

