### Treatment

Treatment consists of the usual treatment-offer provided by the addiction care organizations to maximize ecological validity of the study outcomes. We will document the type of treatment received for SUD, which in the Netherlands mostly consists of integrated cognitive behavioral therapy plus motivational interviewing (CBT + MI), community reinforcement approach (CRA), family therapy, and CBT-based e-health interventions. In addition, we will document – psychosocial and/or pharmacological – treatment for comorbid mental health problems as well as intensity (inpatient; outpatient) and actual duration (retention) of treatment, and type of treatment termination (premature/planned).

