**Index treatment characteristics**					
• Type, intensity, duration of current treatment received and initial treatment response^a^			X		

*DASS-21* Depression, Anxiety and Stress Scale, *MATE-Y* Measurements in the Addictions for Triage and Evaluation – Youth version, *PQ-16* Prodromal Questionnaire – 16 item version, *SCIL* Screener for Intelligence and Learning disability, *SURPS* Substance Use Risk Profile Scale, *VBDM* Valued-based decision-making battery, *WHODAS-2.0* World Health Organization Disability Assessment Schedule, *YIT-*Q Youth In Transition Questionnaire

^a^Note: All information at the end of treatment assessment will be obtained from the responsible clinician

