### Power considerations

Using a sampling fraction of 10% to obtain a representative sample from the total target population (*N* = 4169; see ‘Participants and setting’ above), we aim to include 420 youth in our study. Concerning our first study question, we assume a 30% persistence rate of moderate to severe SUD in our study sample [20, 21, 52]. With precision at 5% [53], a minimum sample size of *N* = 300 would be sufficient to estimate the assumed 30% persistence rate with a 95% level of confidence [54].

However, for our prediction analyses of persistent SUD (study questions 2, 3 and 5) we need a larger sample size than N = 300 to allow a sufficiently large number of predictor variables to be included in the logistic regression models. To avoid overfit of a logistic regression model, authors recommend a minimum of 10 events (i.e., 10 patients with persistent SUD) for each predictor variable [55–57]. Hence, given the assumed 30% persistence rate, and *N* = 420, a maximum of 12 predictor variables could be included in the multivariate logistic regression analysis.

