We will use existing data from the Tracking Adolescents’ Individual Lives Survey (TRAILS) study to investigate the rate of persistent substance dependence (DSM-IV) and its predictors from adolescence to young adulthood in the general population. TRAILS is a prospective cohort study (*N* = 2230) into the development of mental health from preadolescence (age 11 years) to adulthood (up to age 26 years) in the Dutch general population with five biennial or triennial follow-up waves [58]. Candidate-predictors stem from the areas of: demographic background; substance use and SUD; non-SUD mental disorders; family history; life events; and social functioning (see first six domains in Table 1). Logistic regression will be used to investigate the relation of these predictors with the outcome variable, persistent substance dependence, following the two-step procedure suggested by Hosmer and Lemeshow (2000) [59]. Only variables which are significantly associated with the outcome variable in the first, univariate, step will be entered as candidates into the multivariate (backward) logistic regression model in the second step. Next, we will evaluate the accuracy of the set of combined adolescent risk factors found to predict persistent substance dependence in the TRAILS cohort for predicting persistent DSM-5 moderate to severe SUD among youth in addiction treatment, in terms of sensitivity, specificity, and positive and negative predictive value.
(3)Can we optimize the accuracy of predicting persistent DSM-5 moderate to severe SUD among youth in addiction treatment by extending or modifying the general population-based set of predictors with baseline indicators from our addiction treatment sample?

This question will be addressed (a) by building a new prediction model based upon the same potential predictor variables as used in the TRAILS analysis above, and supplement these with potential predictor variables assessed at baseline in our addiction treatment sample (Table 1), and (b) by comparing the accuracy of this treatment-based prediction model with the TRAILS-population-based prediction model.
(4)Which longitudinal treatment outcome trajectories can be identified from adolescence to young adulthood pertaining to substance use and SUD, comorbid mental health problems, and social functioning among youth in addiction treatment?

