Concerning the fourth study question, we will use the total count of DSM-5 SUD-symptoms derived from the MATE-Y, and the sum score on the DASS-21 (mental health problems) and WHODAS 2.0 (social functioning), assessed at baseline and at two- and four-years follow-up (Table 1). To describe the longitudinal course of SUD, mental health problems and social functioning we will employ latent growth curve modeling [60].
(5)Which treatment interventions – in terms of type, intensity and duration – are associated with favorable or unfavorable long-term outcomes, in terms of substance use and SUD, mental health problems and social functioning, for which youth in addiction treatment?

The fifth study question will be answered in two successive steps. First, we will determine which treatment interventions are associated with a favorable treatment outcome, using the same two-step logistic regression procedure as described for study question 3. Next, we will determine whether the youth-related potential predictors for persistent SUD (see study question 3) moderate the favorable or unfavorable long-term outcomes of the different treatment interventions. To determine which treatment interventions are associated with a favorable long-term – two- and four-years – outcome, we will categorize the treatment received along the following dimensions: type of treatment; intensity; duration; type of termination (see section ‘Treatment’ above).

All study questions will be analyzed using the statistical software packages of SPSS version 25, R, and Mplus, where appropriate.

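### Study question 5: backward selection over treatment type together with actual duration and type of termination can hide the part of a type association that runs through retention, and can credit retention with what comes from early response

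*Protocol article*

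**What the plan says.** Question 5 is one of the five primary questions listed under Study objectives. It asks which interventions, by type, intensity and duration, are associated with long-term outcome, and for which youth.

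The Data analysis section gives the method: "First, we will determine which treatment interventions are associated with a favorable treatment outcome, using the same two-step logistic regression procedure". It then sets out the exposures: "we will categorize the treatment received along the following dimensions: type of treatment; intensity; duration; type of termination". The sentence refers back to question 3, but the two-step procedure itself is spelled out under question 2. Variables that are significant one at a time "will be entered as candidates into the multivariate (backward) logistic regression model in the second step".

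The Treatment section says what two of the four dimensions are: "actual duration (retention) of treatment, and type of treatment termination (premature/planned"). Table 1, under index treatment characteristics, has the clinician report at end of treatment on type, intensity and "duration of current treatment received and initial treatment response". The analysis text for question 5 gives that response no role.

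The Discussion calls the data correlational and open to confounding, and promises to include well-known confounders such as socioeconomic status.

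**The concern.** Type and initial intensity can be known when treatment starts. Retention and manner of ending cannot. Two things follow if all four are candidates in one backward model.

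- **Retention as a route.** If one type does better partly because it keeps youth in treatment, holding retention fixed takes that part away. The model may then drop type and keep its consequence.
- **Retention as a marker of course.** A youth who is doing badly early may leave early and also do badly later. Premature ending then goes with persistence even if staying longer changes nothing.

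Conditioning on retention can also produce a type association where there is none, when type affects length of stay and early response affects both stay and outcome. Adjusting for baseline confounders repairs none of this, because the trouble arises after baseline.

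The results would be read as guidance on which treatment to offer and whether to prolong it, which is what question 5 is about.

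**Working it through.** **The plan's own figure.** Power considerations allows at most 12 predictors in the logistic models for questions 2, 3 and 5. With N = 420, 30% persistence ("we assume a 30% persistence rate of moderate to severe SUD in our study sample") and 10 events per predictor: 420 × 0.30 = 126 events, and 126 / 10 = 12.6, rounded down to 12. The figure reproduces. It does not bear on this point, which is about which variables share a model.

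All path strengths below are assumptions. The article gives none. Persistence is taken as the unfavourable outcome.

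**Example 1: type acts only through completion.** Persistence is 18% in completers and 45% in non-completers, whatever the type.

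- Type B, 70% complete: 0.70 × 18% + 0.30 × 45% = 26.1%.
- Type A, 50% complete: 0.50 × 18% + 0.50 × 45% = 31.5%.
- Overall OR for B against A: (0.261/0.739) / (0.315/0.685) = 0.77.
- If A has 40% completion: 0.40 × 18% + 0.60 × 45% = 34.2%, and the OR is (0.261/0.739) / (0.342/0.658) = 0.68.
- Given termination, the OR for type is 1.0. This is built into the example and is not a finding.

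**Example 2: termination has no effect.** Assume 40% relapse early. Persistence is 50% in relapsers and 16.7% in the others, so overall 0.4 × 0.50 + 0.6 × 0.167 = 30%. Premature stopping occurs in 60% of relapsers and 30% of the others.

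- Premature: 0.4 × 0.6 + 0.6 × 0.3 = 0.42 of all youth. Persistent among them: 0.24 × 0.50 + 0.18 × 0.167 = 0.15. Rate 0.15/0.42 = 36%.
- Planned: 0.58 of all youth. Persistent: 0.30 − 0.15 = 0.15. Rate 0.15/0.58 = 26%.
- OR = (0.15/0.27) / (0.15/0.43) = 1.59.
- With 50% against 30% stopping prematurely: (0.13/0.25) / (0.17/0.45) = 1.38.
- Range with overall persistence held at 30% and stopping at 60% against 30%: 20% relapsers with 40% persistence (others 27.5%) gives (0.114/0.246) / (0.186/0.454) = 1.13. With 40% relapsers and 60% persistence (others 10%) it is (0.162/0.258) / (0.138/0.442) = 2.01.

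**Simulation of the two-step procedure.** Two types in equal shares, 30% persistence, ORs from 400,000 subjects, and 500 samples of 420 with p < 0.05 assumed at both steps. Response and duration have residual standard deviation 1. Where a path is present: type to response 0.8, type to duration 0.8, response to duration 0.7, response to log-odds of persistence −0.7. Duration to log-odds is −0.7 in row B only, and direct type to log-odds is −0.6 in row C only. Except in row B, an unmeasured baseline factor acts on response (0.5) and on the log-odds (−0.3).

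| Assumed paths | Type OR alone | Type OR with duration and termination | Type passes step 1 | Type in final model |
|---|---|---|---|---|
| A: type acts through response, response drives duration | 0.61 | 0.75 | 57% | 20% |
| B: type acts only through duration | 0.60 | 1.00 | 63% | 4% |
| C: type acts directly only | 0.59 | 0.58 | 64% | 61% |
| D: type affects duration, not outcome | 1.00 | 1.37 | 4% | 2% |
| E: type affects both response and duration | 0.61 | 1.03 | 57% | 2% |

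In A, C, D and E duration has no effect on outcome. It still receives an OR of 0.67 per unit and stays in the final model in 98–99% of samples. In row D the false OR of 1.37 appears once duration is in the model, but the univariate screen lets it through to the final model in only 2% of samples.

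**The case against.** - **Association, not effect.** Question 5 is worded as association and the Discussion admits confounding. This stands and softens the point: the fault bites when results are read as effects of type or of longer stay. But a type association given retention still answers a different question from the association of type as offered.
- **Joint entry is a reading.** The article lists four dimensions and one procedure, and the final model may be specified elsewhere. Joint entry is the most natural reading, and nothing in the text keeps duration and termination apart from type.
- **The univariate step already gives a type estimate free of duration.** True, but it is a screen, unadjusted for baseline. In Example 1, with 420 youth in two equal groups and a 5% level, type would pass that screen in only about 23% of samples (44% in the 40% against 70% variant). Much of the loss there would come from limited power, before any backward step.
- **Dependence of retention on type and response is inferred.** Correct. The words retention and premature make it plausible, but the article does not say it.

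A reader might infer that the model removes the effect of type altogether. It does not: row C shows a direct association left intact. A reader might also infer an error in counting follow-up from entry, since treatment beyond 12 months would overlap the past-year window of the 2-year outcome. Follow-up from entry is the declared design, and the article gives no treatment durations, so there is no basis for calling the overlap common or a fault.

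**Conclusion.** The point holds in limited form. As written, the plan lets backward selection choose between treatment type and variables realised after entry. Neither the general confounding caveat nor baseline covariates deal with that.

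The part of a type association that runs through retention or response can be lost: from an OR of about 0.6 to between 0.75 and 1.03 in scenarios A, B and E, with type in the final model in 2–20% of samples. Retention or planned completion can be credited with an association that belongs to early response: OR 1.59 for premature stopping in Example 2, about 1.1 to 2.0 across other assumed inputs. A false type association is possible but would seldom survive the univariate screen in the case simulated.

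Every one of these sizes rests on assumed paths. They show what can happen, not what will. The change is worth making before analysis because question 5 is a primary question.

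**What to change.** In the question 5 text of the Data analysis section:

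- Estimate the associations of type and initial intensity with long-term outcome in a model with baseline covariates only, outside any backward selection that includes duration or termination. Specify initial intensity, since Table 1 records treatment received at end of treatment and intensity may have changed by then. Confirm that the starting type and intensity can be recovered from that record.
- Analyse duration separately. One way is a landmark: at a fixed time after entry, compare youth still in treatment with those who have stopped, adjusted for baseline. State that the recorded initial response may explain any difference.
- Report type of termination descriptively, as an intermediate outcome.
- Do not exclude youth whose treatment runs into the outcome window, because that selects on post-entry duration. At most, report how many there are.

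Cost: a change of wording and a little more analysis. Actual duration and termination are already to be documented. The landmark analysis loses the information before the landmark.

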## Study objectives

In this study, we will investigate the rate of persistent SUD and its predictors longitudinally from adolescence to young adulthood in a representative treatment sample of youth with DSM-5 SUD from the start of their addiction treatment to 2 and 4 years following treatment-entry. In addition to SUD, we will investigate the course of comorbid mental disorders and social functioning, and their relation with SUD over time.

Our primary study questions are:
What is the persistence rate of DSM-5 moderate to severe SUD from adolescence to young adulthood among youth in the two and four years following entry in addiction treatment?What is the prognostic value of a general population-based set of predictors of persistent SUD – based on the Dutch Tracking Adolescents’ Individual Lives Survey (TRAILS) study – from adolescence to young adulthood for predicting persistent DSM-5 moderate to severe SUD among youth in addiction treatment?Can we optimize the accuracy of predicting persistent DSM-5 moderate to severe SUD among youth in addiction treatment by extending or modifying the general population-based set of predictors with baseline indicators from our addiction treatment sample?Which longitudinal treatment outcome trajectories can be identified from adolescence to young adulthood pertaining to substance use and SUD, comorbid mental health problems, and social functioning among youth in addiction treatment?Which treatment interventions – in terms of type, intensity and duration – are associated with favorable or unfavorable long-term outcomes, in terms of substance use and SUD, mental health problems and social functioning, for which youth in addiction treatment?

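### Study question 5 covers three outcome areas but names only logistic regression on a favorable outcome, so the DASS-21 and WHODAS 2.0 scores are either cut at an unstated point or not analysed

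*Protocol article*

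**What the plan says.** All places are in the protocol article.

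- **Study objectives and Data analysis, question 5.** The question is which treatments "are associated with favorable or unfavorable long-term outcomes, in terms of substance use and SUD, mental health problems and social functioning". Study objectives lists it among the primary study questions.
- **Data analysis, question 5, first step.** "we will determine which treatment interventions are associated with a favorable treatment outcome, using the same two-step logistic regression procedure". The text refers back to question 3 for this procedure; the steps themselves are set out under question 2: "Only variables which are significantly associated with the outcome variable in the first, univariate, step will be entered as candidates", followed by a backward multivariable logistic model. The second step of question 5 tests whether youth characteristics moderate the results.
- **Data analysis, question 4.** Besides the SUD symptom count, the outcome measures are "the sum score on the DASS-21 (mental health problems) and WHODAS 2.0 (social functioning), assessed at baseline and at two- and four-years follow-up". The model is also named: "To describe the longitudinal course of SUD, mental health problems and social functioning we will employ latent growth curve modeling".
- **Power considerations.** "for our prediction analyses of persistent SUD (study questions 2, 3 and 5) we need a larger sample size than N = 300". Here question 5 is described as an analysis of persistent SUD, which Data analysis defines as a binary outcome.

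The question 5 text does not name the DASS-21 or the WHODAS 2.0. It gives no definition of a favorable result in mental health or social functioning, and it names no model other than logistic regression.

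**The concern.** Two adjacent paragraphs handle the same constructs in ways that do not fit together. Question 4 treats mental health problems and social functioning as repeated scores. Question 5 takes up the same areas with a model class that accepts only a yes/no outcome.

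If the scores are cut to fit the model, precision is lost and the answer depends on where the cut is placed. If they are not analysed, a primary question is answered for one of its three areas. The first case matters most in the second step of question 5: moderator tests usually have less power than main comparisons, and the protocol gives no power figure for these outcomes.

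**Working it through.** **1. The plan's own figures.** Precision for a 30% rate, ±5%, 95% confidence: 1.96² × 0.30 × 0.70 / 0.05² = 322.7. With the finite population correction for 4169: 322.7 / (1 + 321.7/4169) = 299.6, so the stated 300 reproduces. Events per predictor: 420 × 0.30 / 10 = 12.6, so the stated maximum of 12 reproduces. Both figures concern persistent SUD. Neither says anything about the DASS-21 or WHODAS 2.0.

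**2. The two readings of question 5.**

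| Reading | Basis in the text | Consequence |
|---|---|---|
| Logistic regression covers all three areas | Wording of the question | If the question 4 measures are used, the sum scores must be cut; no cut is stated |
| Logistic regression covers persistent SUD only | Power considerations; cross-reference to question 3 | Mental health and social functioning have no question 5 analysis |

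**3. Cost of cutting a score, first reading.** For a normal score and a shift in mean, the efficiency of the binary version relative to the score is φ(z_q)² / [q(1 − q)], where q is the proportion on one side of the cut. The sample size of 420 is the protocol's; normality and the cuts are assumptions.

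| Cut | Efficiency | Loss | Information in 420, as number of youth |
|---|---|---|---|
| 50/50 | 0.1592 / 0.25 = 0.637 | 36.3% | 267 |
| 30/70 | 0.1209 / 0.21 = 0.576 | 42.4% | 242 |
| 20/80 | 0.0784 / 0.16 = 0.490 | 51.0% | 206 |

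The median cut is the best case for a normal score (loss 1 − 2/π).

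**4. Sensitivity to the shape of the score.** The comparison is with an analysis of means, and the general formula for a shift is f(x_q)² × variance / [q(1 − q)].

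| Assumed score and effect | Loss, median cut | Loss, cut at 70th percentile |
|---|---|---|
| Logistic, shift | 17.8% | 30.9% |
| t with 10 df, shift | 24.3% | 34.4% |
| t with 5 df, shift | 3.9% | 20.5% |
| Gamma shape 4, shift | 29.6% | 54.9% |
| Gamma shape 1, shift | 0% | 57.1% |
| Gamma shape 4, proportional effect | 40.6% | 36.1% |
| Gamma shape 1, proportional effect | 52.0% | 37.9% |

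In extreme shapes the cut can even beat the mean (Laplace, median cut: efficiency 2.0). So 36% is a floor under normality and not in general.

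**5. What this means for power (illustration).** Assumed: two treatment groups of 210, standardised difference 0.30, two-sided 5%, no dropout. Power is 86.7% for the score, 68.7% after a median cut and 64.2% after a 30% cut.

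**6. Role of the baseline score (simulation).** Assumed: n = 420 in two equal groups, difference 0.25, baseline–follow-up correlation 0.5, median cut. Baseline-adjusted linear regression has about 83% power. Logistic regression on follow-up status has about 49%, or about 58% with the baseline score as a covariate. Adjusting the logistic model recovers only part of the loss.

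**The case against.** The strongest reply is that the protocol never says it will cut the DASS-21 or WHODAS 2.0. Those sum scores are introduced for question 4 only. The question 5 procedure is borrowed from question 3, whose outcome is persistent SUD, and Power considerations says the same. On that reading no score is cut and no information is lost. This stands against any statement that dichotomisation is planned. It does not rescue question 5, because two of its three areas are then left without an analysis.

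Second, Table 1 contains measures in both areas that are not sum scores, such as past-year mental disorders, employment and living arrangements. Logistic regression could be applied to some of these without cutting a scale. That stands as a possibility, but the text does not say it, and question 4 chose the sum scores to represent these areas.

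Third, a reader might infer that the baseline scores are ignored. The documents do not support this: question 3 draws candidate predictors from the baseline measures in Table 1, which include both scales, and the Discussion promises adjustment for known confounders. Baseline adjustment is possible, though not fixed.

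Fourth, a reader might infer that at least a third of the information is necessarily lost. That requires roughly normal scores, and the protocol gives neither distribution nor cut-off.

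Finally, the definition of favorable may be left to a fuller plan. That is fair for the cut-off. But this article states a binary model class, and a later cut-off would not change that.

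**Conclusion.** The point holds as a mismatch between question and method. Question 5 spans three areas, and the one model named for it suits persistent SUD but does not fit the sum scores by which question 4 represents the other two. Which consequence follows depends on a reading the text leaves open: scores cut at an unstated point, or two areas without a matching analysis.

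The size applies only to the first reading. For roughly normal scores the loss is about 36% at best and about 42% at a 30/70 split, so 420 youth carry the information of about 267 or 242. Heavy-tailed scores can lose less, and some skewed scores lose more. The power figures also rest on assumed effect sizes, equal groups and an assumed baseline correlation. No loss is claimed for persistent SUD, which is binary by definition.

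**What to change.** Keep logistic regression for persistent SUD. For the other two areas of question 5, state that the DASS-21 and WHODAS 2.0 sum scores at 2 and 4 years are analysed as continuous outcomes, by one of two routes:

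- a linear mixed model with the baseline score of the same scale as covariate and the treatment dimensions (type, intensity, duration, termination) as explanatory variables; or
- the question 4 latent growth model extended with those treatment covariates.

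Any favorable/unfavorable split of these scores then becomes a supplementary description. If question 5 is meant to concern persistent SUD only, its wording in Study objectives and Data analysis should be narrowed to say so.

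The cost is plan wording and slightly more analysis work. The repeated measures are already in Table 1, and R and Mplus are already named. The price in interpretation is that the main result for these two areas is a mean score difference and not an odds ratio for a favorable outcome.

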## Discussion

This study aims to investigate the long-term course of SUD, concurrent mental health problems and social functioning in a group that is particularly at risk for chronicity: youth in addiction treatment. Strengths of the study are (1) obtaining a nationally representative sample of youth in addiction treatment, (2) the relatively large size of our cohort, (3) the use of both self-report and endophenotypical biological and cognitive-behavioral data, and (4) our aim to determine the long-term outcome of youth addiction treatment in a naturalistic, ‘real world’ treatment context. Study limitations include the following. First, our study sample consists of youth aged 16 to 22 years. We would have preferred to include younger adolescents as well, but Dutch national registration data showed that only 618 youths aged 15 years and younger seek help at addiction treatment annually (i.e., 11% of total youths’ treatment demand). Second, our maximum follow-up period is 4 years. We would have preferred a longer follow-up period (e.g., 8 to 10 years) to sufficiently cover the age of young adulthood, but this was not possible due to budget limitations. Third, our study data are in essence correlational in nature, and hence, are subject to confounding. Including a non-treatment control group would limit confounding, but for reasons of feasibility, ethics and costs, we chose not to include a non-treatment (matched) control cohort in our study. Another option would have been to conduct a large-scale randomized controlled trial (RCT), but for obvious reasons an RCT with a non-treatment control group would be unacceptable for ethical reasons. Nevertheless, we will include important and well-known confounders like social economic status in our analyses. Lastly, most of our data are based on self-report and may be subject to underreporting. Self-reported substance use can be verified by means of urinalyses, but this method only provides a momentary assessment and does not give an indication of amount or severity of use. Studies indicate that self-report is quite reliable if confidentiality is guaranteed and if no negative consequences are attached to the answers provided by the person [61, 62]. To assure that this will be the case, our study assessments will be conducted by research-assistants that are independent from treatment-staff. Nevertheless, youths with insufficient comprehension of basic Dutch language will be barred from the study (exclusion criterion), and hence this potentially important subpopulation will not be represented in our study data.

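### Study question 5 screens the treatment variables on their crude significance, so a helpful treatment given more often to severe youths can be dropped before any adjusted effect is estimated

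*Protocol article*

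**What the plan says.** Question 5 asks which treatment interventions, by type, intensity and duration, go with good or poor long-term outcome, and for which youths. The Data analysis section gives two stages. In the first, "we will determine which treatment interventions are associated with a favorable treatment outcome, using the same two-step logistic regression procedure". The variables submitted to it are the treatment descriptors: "we will categorize the treatment received along the following dimensions: type of treatment; intensity; duration; type of termination". In the second, youth-related predictors are examined as moderators of treatment outcome.

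The text points to question 3 for the procedure, but the only two-step logistic procedure in the article is written under question 2, for the TRAILS predictors. Its entry rule is: "Only variables which are significantly associated with the outcome variable in the first, univariate, step will be entered as candidates into the multivariate" model, which then uses backward selection. The significance level for entry is not stated. Nothing exempts the treatment variables from either step.

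On allocation, the Research design section says: "Treatment consists of treatment as usual, as provided by the participating addiction care organizations". The Discussion concedes that "our study data are in essence correlational in nature, and hence, are subject to confounding" and adds that "we will include important and well-known confounders like social economic status in our analyses". It does not name baseline severity of the disorder there.

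**The concern.** A univariate screen is a way of thinning a long list of candidate predictors. In question 5 the treatment variables are the exposures whose association with outcome is the question itself. Under the stated rule an exposure receives an adjusted estimate only if its unadjusted one is already significant.

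In usual care, severity can influence what a youth receives. If severe youths, who are more likely to have a persistent disorder, more often get a helpful treatment, the crude association is pulled towards no effect and may cross it. The treatment then fails the screen, although the adjusted model would have been able to show the benefit. Confounders entered at step 2 cannot help an exposure removed at step 1. At stake is a report that an intervention is unrelated to outcome when the study's own data, properly adjusted, would have indicated a benefit.

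**Working it through.** **The plan's own figures.** Power considerations gives N = 420, 30% persistence and 10 events per predictor: 420 × 0.30 = 126 events, and 126 / 10 = 12.6, hence the stated maximum of 12. The stated N = 300 for question 1 also reproduces: 1.96² × 0.3 × 0.7 / 0.05² = 322.7, and with the finite-population correction for 4169, 322.7 / (1 + 321.7 / 4169) = 299.6. Neither figure is in dispute. The 12-predictor limit matters for the fix.

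**Simulation of the screen.** From the document: N = 420 and 30% persistence. Assumed: 30% of youths receive the treatment, severity S ~ N(0,1) is measured without error, there is no other confounder, and follow-up is complete.
- Allocation: logit P(treated) = a + g·S, with g set to give the severity gap between treated and untreated.
- Outcome: logit P(persistent) = c + 0.7·S + log(OR)·treated, that is, a severity OR of about 2 per SD.
- The intercepts a and c are set to give 30% treated and 30% persistent.

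A treatment is dropped if its crude p-value is at or above the screen level. Power is the share of studies in which the severity-adjusted model that keeps the treatment shows benefit at p < 0.05.

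True OR 0.5:

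| Severity gap | Dropped, 0.05 screen | Dropped, 0.25 screen |
|---|---|---|
| none | 26% | 7% |
| 0.2 SD | 44% | 16% |
| about 0.5 SD | 73% | 38% |
| about 0.7 SD | 88% | 61% |

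Adjusted power is about 76–80% in every row. The crude OR is about 0.72 at the 0.5 SD gap and 0.83 at 0.7 SD. At those gaps the 0.05 screen discards a treatment whose adjusted effect is significant in about 49% and 65% of studies. Repeat runs agree to within about 3 percentage points.

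With a weaker true OR of 0.6 and a gap of about 0.5 SD, the crude OR is 0.85, about 90% are dropped at 0.05 (62% at 0.25), and adjusted power is 52%.

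**Second construction, checkable by hand.** Assume severity is binary with 50% severe, severity OR 3, true treatment OR 0.5, and treatment given to 30% of mild and 70% of severe youths. Overall 0.5 × 0.3 + 0.5 × 0.7 = 50% are treated, or 210 per group. The crude OR is 0.79.
- With 30% persistence overall, an OR of 0.79 corresponds to risks of 0.275 (treated) and 0.325 (untreated), so the cells are about 57.8, 152.2, 68.2 and 141.8.
- SE(log OR) = √(1/57.8 + 1/152.2 + 1/68.2 + 1/141.8) = 0.2135.
- z = ln(0.79) / 0.2135 = −0.2357 / 0.2135 = −1.10.
- Chance of passing a 0.05 screen ≈ Φ(1.10 − 1.96) = Φ(−0.86) ≈ 0.20.

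Simulation gives 20% passing, against 84% power for the severity-adjusted model. With equal allocation (50% treated in both strata), 86% pass and adjusted power is 87%. The loss therefore comes from confounding and not from the screen alone.

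**The case against.** Several counter-arguments deserve weight.

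- *The loss is contingent.* The protocol does not say that severity drives allocation, or how strongly; its Treatment section lists treatments without linking any to severity. This stands. A reader might infer that a beneficial treatment given to severe youths will be discarded; the document supports only that it can be, and that under moderate confounding it often would be.
- *The screen level is unstated.* Correct. A lenient level such as 0.25 roughly halves the loss at a 0.5 SD gap (73% to 38%) but does not remove it.
- *The moderation stage may bring treatments back.* It refers to the different interventions without limiting them to survivors of the screen. That leaves the matter open, so one cannot say a dropped treatment never appears in an adjusted model. But the text does not say that it returns, and a moderation model addresses interaction, not the adjusted main effect.
- *The rule applies only by cross-reference, and the reference is loose.* True, but there is no other two-step logistic procedure to which it could refer.
- *Confounders are promised, and question 5 claims only association.* The promise cannot reach a variable removed at step 1, and the commitment to adjust shows that crude association is not what the investigators want to report.
- *The adjusted power is optimistic.* It assumes one perfectly measured confounder, no other covariates, complete four-year follow-up and no clustering by organisation. This stands.

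A reader might also infer that the screen yields a false list of favourable treatments favouring those given to milder youths. That is not shown: such a treatment may pass step 1 more easily, but step 2 would adjust it unless severity were absent from, or eliminated in, that model. The demonstrated harm is missed benefit.

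**Conclusion.** The point holds as a defect in a stated rule, not as an omitted detail. Applying crude-significance entry to the exposures of interest, in non-randomised usual care, can remove a helpful treatment before its adjusted main effect is estimated, and the confounder commitment in the Discussion does not repair this.

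The size depends on how far severity governs treatment. It is essentially nil without a severity gap, modest at 0.2 SD, and large at 0.5 SD or more, where a 0.05 screen loses the treatment in roughly three quarters or more of studies under a true OR of 0.5. These are illustrations: only N = 420 and 30% persistence come from the protocol. The change should be made before the question 5 analysis, but the other study questions do not depend on it.

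**What to change.** State that in question 5 the treatment variables bypass both the univariate screen and backward elimination. Estimate each treatment dimension in its own model, adjusted for a short prespecified set of baseline confounders that includes baseline severity of the disorder, which the MATE-Y already provides. Keep each model within the 12-predictor limit. Report every adjusted odds ratio with its 95% confidence interval, significant or not, with the crude estimate beside it. Correct the pointer to the two-step procedure, and say which treatments enter the moderation stage.

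Do not put all dimensions into one model. On one count, four main treatment types (3 terms), two kinds of comorbidity treatment (2), and intensity, duration and termination (3) use 3 + 2 + 3 = 8 of the 12 predictors, leaving 4 for confounders. Duration and termination also arise after baseline and may lie on the path from treatment type to outcome, so treatment type should not be adjusted for them. Analyse those two separately and interpret them with caution.

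The cost is a few sentences in the analysis plan, more models to report and somewhat wider intervals. Residual confounding remains and should be acknowledged.
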